### 2.4. Study Design

Children between 1 and 59 months with acute watery diarrhea, presenting to the KH, with a stool sample that is positive for Shigella according to the RLDT, will be enrolled in the study (named the NDSD group). For comparison, a second group of children with dysentery (presence of visible blood in stool) and positive for Shigella according to the RLDT (DS group) will be included (see enrolment flow chart in Figure 1). The DS group will be treated with antibiotics as a standard treatment. A third group of children with watery diarrhea negative for Shigella according to the RLDT (WD group) will also be enrolled. All RLDT-positive stool samples and 10% of the RLDT-negative stool samples selected at random will be confirmed for Shigella via culture analysis. All RLDT-positive stool samples will be re-tested by qPCR.

Following enrolment, the children in all three groups will be evaluated and compared based on the following factors to assess morbidity: whether requires hospitalization (inpatient), the severity of their diarrhea (the number of loose stools per day, the presence of sunken eyes, the loss of skin turgor, and whether intravenous hydration is required), other clinical symptoms (fever, rectal straining, abdominal pain and cramp, anorexia, convulsion, vomiting, etc.), the length of their illness, and their diarrheal severity score [21]. The duration of the shedding of Shigella bacteria in stool following the index diarrhea episode will be evaluated using stool samples collected on every other day until day 14 and then twice per week tested by the RLDT and culture until two consecutive stool samples are negative for Shigella by the RLDT.

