### 2.6. Collection, Preparation, and Archiving of Biological Samples

Stool and blood specimens will be collected at the baseline during enrolment at the hospital by the study staff and during follow-up home visits by the field staff following the schedule (Table 1) to evaluate inflammatory and immune markers. Gut barrier function will be assessed using the lactulose rhamnose (LR) permeability test, wherein urine will be collected before, 2 h after, and 5 h after the administration of LR solution to determine the ratio of L:R among the study children. Using blood serum, we will measure C-reactive protein, intestinal fatty-acid-binding protein, lipopolysaccharide, and flagellar (FliC) IgA and IgG levels to measure systemic inflammation, enterocyte death, and the translocation of pathogens. We will monitor gut inflammation by measuring the levels of myeloperoxidase (MPO) and lactoferrin (LF) in stool samples. The panel of 10 inflammatory cytokines (IL-2, -4, -6, -8, -10, -13, -1ß, TNF-α, IFN-γ, IL-17) will be tested in both serum and stool samples. Other major enteric pathogens will be detected in stool using quantitative PCR. All samples will be collected, processed, and stored following the standard operating procedures developed in the study protocol and following the schedule of events (Table 1).

In order to evaluate whether the RLDT could be implemented in a rural primary healthcare hospital in Bangladesh, we will train the hospital staff in the RLDT procedure and certify them. During the screening for enrolment in the INSIGHT study, 225 randomly selected stool samples will be sent to the rural hospital lab to be rescreened with the RLDT by the trained hospital staff, independently. The results will be compared with the RLDT results that were obtained by the INSIGHT study staff for the purpose of enrolling participants. We will determine the level of technical support needed for the RLDT, its ease of use, and its acceptability among the hospital lab staff using a questionnaire.

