The magnitudes and kinetics of the inflammatory markers will be compared at enrolment and over the follow-up period between DS cases and NDSD cases. Analyses for comparisons of dichotomous outcomes, such as fold increases/decreases in the markers from baseline, will be performed with the chi-square test or Fisher’s exact test if cell counts are sparse. For comparisons of the levels at a specific day between the two groups, a student’s *t*-test will be performed. MPO and LF data will be adjusted for breastfeeding. The data from the cases and their matched controls will be evaluated using paired *t*-tests. Linear regression analysis results will be compared between cases and controls adjusting for anthropometry and cognitive developmental changes, future diarrhea episodes, and antibiotic use in the follow-up period, and sociodemographic risk factors for inflammation.

For the RLDT evaluation at the rural primary healthcare facility, the RLDT results from the hospital staff will be compared with the results from the INSIGHT study staff (gold standard), analyzing sensitivity, specificity, and positive and negative predictive values. We will also use pairwise comparisons with Cohen’s kappa (measuring the agreement between binary outcomes +/− of tests without requiring a gold-standard).

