Regarding the management of diarrhea, although the WHO recommends antibiotics only for children with bloody diarrhea, over 40% of children with non-bloody watery diarrhea currently receive antibiotics as part of non-standard treatment in low- and middle-income countries [33]. This overuse of antibiotics contributes to the development and spread of antimicrobial resistance, both at the individual level and at the population level. If the INSIGHT study determines that NDSD cases should be treated with antibiotics to improve the survival and long-term developmental potential of children with this condition, the identification of such cases will require a rapid test to document these infections so that treatment can be evidence-based and initiated promptly.

Shigellosis cannot be distinguished reliably from other causes of bloody diarrhea or other causes of watery diarrhea based on clinical features alone. The most frequently used and the current gold-standard diagnostic method for Shigella is the direct culture method [5,34]. However, recent studies have shown that the culture method is not sufficiently sensitive [8,35]. Moreover, culture analysis takes 2–3 days and is therefore not feasible as a POC diagnostic test. The PCR or quantitative PCR (qPCR) methods are highly sensitive [8,35]; however, these assays are highly dependent on technology and equipment, require improved laboratory facilities and trained personnel, and are time-consuming and expensive. Therefore, the current diagnostic methods in practice are not practical for routine use and are not applicable in most healthcare settings where Shigella infections are endemic. The INSIGHT study will evaluate the performance and implementation of the simple, rapid, and sensitive RLDT assay for Shigella in a primary healthcare facility in Bangladesh in order to determine if the RLDT could be used as a potential diagnostic tool to rapidly detect and treat shigellosis. Identifying children with shigellosis and developing targeted treatment strategies for these children may potentially lower antimicrobial resistance.

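### The RLDT evaluation calls the study-staff RLDT a gold standard, so its sensitivity, specificity and predictive values are operator agreement labelled as accuracy for Shigella

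*Protocol article*

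**What the plan says.** Section 2.6 describes the exercise: "225 randomly selected stool samples will be sent to the rural hospital lab to be rescreened with the RLDT by the trained hospital staff, independently". It then names the comparator: "The results will be compared with the RLDT results that were obtained by the INSIGHT study staff for the purpose of enrolling participants". Section 3.2 labels that comparator: "the RLDT results from the hospital staff will be compared with the results from the INSIGHT study staff (gold standard"). The measures against it are given as "analyzing sensitivity, specificity, and positive and negative predictive values". Section 3.2 continues: "We will also use pairwise comparisons with Cohen’s kappa", and describes kappa as agreement that needs no gold standard.

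Section 3.1 sizes the exercise at 225 samples, of which 45 are described as subjects with Shigella, at a disease prevalence of about 20%. It claims 80% power for sensitivity and 100% for specificity (0.60 versus 0.80, two-sided binomial test), with actual significance levels of 0.0336 and 0.0397.

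Two other places bear on the label. The Discussion names direct culture as the current gold-standard method, adds that culture is not sensitive enough, and says that the study "will evaluate the performance and implementation of the simple, rapid, and sensitive RLDT assay". Section 2.4 plans culture for all RLDT-positive stools, says that "10% of the RLDT-negative stool samples selected at random will be confirmed for Shigella via culture analysis", and plans qPCR for the RLDT-positives only.

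**The concern.** Sensitivity and specificity mean accuracy only when the reference establishes, independently of the test, whether Shigella is present. Here the reference is the test itself, run by other hands. If the assay misses an infection in both runs, the sample counts as a correct negative. If it gives a false positive in both runs, the sample counts as a correct positive. If only the study-staff run is wrong, a correct hospital result counts as an error.

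The terms used in sections 3.1 and 3.2 (gold standard, sensitivity, specificity, predictive values, subjects with Shigella, prevalence of the disease) all present the result as accuracy. The Discussion wants to use it to judge whether the RLDT can guide detection and treatment of shigellosis in such facilities. A published sensitivity from a rural facility would be read in that sense, although no sample's Shigella status is set by an independent method in this analysis.

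**Working it through.** **1. Is the comparator the same assay?** Section 2.6 has the index test as the RLDT repeated by hospital staff and the comparator as the RLDT result that study staff obtained for enrolment, on the same samples. Section 3.2 calls the latter the gold standard. The Discussion gives that title to culture. The document thus uses one term for two different references.

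**2. What the planned measures estimate.** Among samples that study staff call positive, the share that hospital staff also call positive is positive percent agreement. The corresponding share among negatives is negative percent agreement. The predictive values are the same agreement conditioned on the hospital result.

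**3. The plan's own figures.** Inputs from section 3.1: N = 225, prevalence 20%, p0 = 0.60, p1 = 0.80, two-sided 0.05. This gives 225 × 0.20 = 45 positives and 225 − 45 = 180 negatives. Exact binomial test with at most 0.025 in each tail:

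| | n | Reject at | Actual alpha | Stated alpha | Power at 0.80 | Stated power |
|---|---|---|---|---|---|---|
| Sensitivity | 45 | ≤19 or ≥34 | 0.0336 | 0.0336 | 82.6% | 80% |
| Specificity | 180 | ≤94 or ≥122 | 0.0397 | 0.0397 | 99.996% | 100% |

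Both significance levels match. The number 45 is the smallest n at which exact power reaches 80% (79.5% at 42, 74.6% at 44), so 80% reads as the target. The arithmetic is sound; only the quantity that it is attached to is mislabelled.

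**4. How far agreement can lie from accuracy.** The documents give no accuracy figures for the RLDT, so the values here are assumptions: prevalence 0.20, true sensitivity Se = 0.85, and true specificity Sp from 0.90 to 1.00, equal for both operators.

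*Shared errors.* If the hospital run reproduces every study-staff result, apparent sensitivity and specificity are both 1.00, whatever Se and Sp are.

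*Errors independent given true status.* Let P = 0.2·Se + 0.8·(1 − Sp) be the proportion that study staff call positive. Then

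- apparent sensitivity = [0.2·Se² + 0.8·(1 − Sp)²] / P
- apparent specificity = [0.2·(1 − Se)² + 0.8·Sp²] / (1 − P)

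For Sp = 0.90: P = 0.17 + 0.08 = 0.25. Apparent sensitivity = (0.1445 + 0.0080) / 0.25 = 0.61, and apparent specificity = (0.0045 + 0.6480) / 0.75 = 0.87.

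| True Sp | P | Apparent sensitivity (true 0.85) | Apparent specificity |
|---|---|---|---|
| 0.90 | 0.250 | 0.61 | 0.87 |
| 0.95 | 0.210 | 0.70 | 0.92 |
| 0.99 | 0.178 | 0.81 | 0.96 |
| 1.00 | 0.170 | 0.85 | 0.97 |

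Shared errors push the figures above the truth. Independent errors leave them at or below it. The real case lies somewhere between, and the planned data cannot show where.

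**5. What independent reference data would exist.** If the 225 samples follow section 2.4, with about 20% RLDT-positive, all 45 positives would have culture and qPCR. About 0.10 × 180 = 18 negatives would have culture, and the plan provides no qPCR for negatives.

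**The case against.** The strongest defence is that the comparator fits the aim. Sections 2.2 and 2.6 ask whether the RLDT can be applied in a rural primary facility: staff are trained and certified, retest independently, and are surveyed on support needs, ease of use and acceptability. For that question, agreement with trained study staff is a legitimate target. The Introduction says that the assay has already been evaluated, the comparator is openly disclosed, kappa is planned, and section 2.4 has its own assay-level confirmation by culture and qPCR. All of this stands, and it makes the point one of labelling and scope, not of a useless comparison. It does not rescue the accuracy terms, the sizing on subjects with Shigella, or the reach of the word performance in the Discussion.

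Three stronger readings are tempting, and the documents support none of them.

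- *The figures are inflated by construction.* That holds only if the two runs share errors. With independent errors the figures fall at or below the truth, as shown above.
- *The sample size is deficient because 225 randomly drawn stools need not contain 45 positives.* With positives distributed as Binomial(225, 0.2), the central 95% range is 34 to 57 and averaged power is 78.4%. That is under two points below target for a secondary evaluation, with prevalence given only as approximate. It is minor.
- *Culture and qPCR could simply replace the comparator.* Positives would then be judged by culture plus qPCR and negatives by culture alone, which the Discussion calls insufficiently sensitive. Infections missed by both the RLDT and culture would count as true negatives and overstate sensitivity.

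**Conclusion.** The point holds as one of mislabelling that affects what may be concluded. Sections 3.1 and 3.2 attach accuracy terms and a gold-standard label to a comparison of the RLDT with itself, in conflict with the Discussion's own statement that culture is the gold standard. That follows from the text alone and needs no assumption.

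No sample size or power figure changes. The size of any error, if the results are read as accuracy, cannot be fixed from the documents. Under the assumed true sensitivity of 0.85 and 20% prevalence, the reported value could lie anywhere from 0.61 to 1.00, depending on specificity and on how far the two runs share errors. The direction is not known in advance. The correction should be made because it concerns a named aim and the evidence on which a deployment argument would rest.

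**What to change.** **Rewording.**

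- Section 3.2: drop the gold-standard label. Report positive and negative percent agreement with the study-staff RLDT, plus the planned kappa. Drop the predictive values, or present them as agreement conditional on the hospital result.
- Section 3.1: state the 0.60 versus 0.80 hypotheses as percent agreement, replace the 45 subjects with Shigella by 45 study-RLDT-positive samples, and describe the 20% as the expected proportion RLDT-positive. The numbers stay as they are.
- Discussion: limit the performance conclusion from this exercise to reproducibility and implementation.

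**Optional secondary analysis.** Compare the hospital RLDT with the culture already planned in section 2.4. Use culture as the reference for positives and negatives alike, weight the cultured negatives for the 10% verification fraction, and state culture's limited sensitivity. With about 18 cultured negatives among the 225, this would be imprecise and should be called descriptive. If accuracy is wanted as a main result, one independent reference on all 225 samples would be needed. The 45/180 calculation would then apply unchanged at 20% prevalence, but with extra laboratory work, mainly on the negatives.

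**Cost.** The rewording costs nothing in samples or laboratory work. The price is that the trial gives up any claim of diagnostic accuracy from the 225-sample comparison.

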## 3. Statistical Considerations

### 3.1. Sample Size and Power

This study’s hypothesis is that the rates of hospitalization (inpatient) will be similar among the NDSD and DS cases. This is a matched set of cases (DS) and controls (NDSD) with two matched controls per case. The second comparison group is the WD group (1:1 matched with case). Based on previous data on the hospitalization rates of shigellosis cases in Mirzapur (obtained via personal communication with [name] et al.), we assume that the probability of hospitalization among the controls will be 20%. Since it is not known, as a general practice, the correlation coefficient for exposure between the matched cases and controls is set to 0.2. If the true odds ratio for hospitalization in the exposed subjects relative to the unexposed subjects is 0.5, we will need to study 123 cases of shigellosis with dysentery with 2 matched controls per case in order to be able to reject the null hypothesis that this odds ratio equals 1 with a probability (power) of 0.8. If the alternative hypothesis is not satisfied, then we will accept the null hypothesis of no difference in hospitalization rates between the cases and controls. The Type I error probability associated with the test of this null hypothesis is 0.05. With an estimated 20% of participants lost to follow-up, we will enroll 148 children each in the DS and WD groups and 296 in the NDSD group (total: 592).

For the RLDT evaluation in the primary healthcare facility, a sample size of 225 (45 subjects with Shigella) achieves 80% power to detect a change in sensitivity from 0.60 to 0.80 using a two-sided binomial test and 100% power to detect a change in specificity from 0.60 to 0.80 using a two-sided binomial test with the target significance level set to 0.05. The actual significance level achieved by the sensitivity test is 0.0336 and that achieved by the specificity test is 0.0397. The prevalence of the disease is ~20%.

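### The primary-care RLDT evaluation measures agreement between two sets of operators of one assay, but is labelled and sized as accuracy for Shigella

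*Protocol article*

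**What the plan says.** Section 2.6 describes the procedure: "225 randomly selected stool samples will be sent to the rural hospital lab to be rescreened with the RLDT by the trained hospital staff". The hospital staff work independently, and their results are set against the RLDT results that the study staff obtained for enrolment. Section 3.2 gives the analysis: "the RLDT results from the hospital staff will be compared with the results from the INSIGHT study staff (gold standard), analyzing sensitivity, specificity", together with positive and negative predictive values. It then adds Cohen's kappa as a measure that needs no gold standard.

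Section 3.1 gives the sizing: "a sample size of 225 (45 subjects with Shigella) achieves 80% power to detect a change in sensitivity from 0.60 to 0.80", and "100% power to detect a change in specificity from 0.60 to 0.80 using a two-sided binomial test". It puts the prevalence of the disease at about 20%.

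Two other places bear on the reference. The Discussion states: "The most frequently used and the current gold-standard diagnostic method for Shigella is the direct culture method". It adds that culture is not sensitive enough and that PCR methods are highly sensitive, and it says the study will evaluate both the performance and the implementation of the RLDT in primary care. Section 2.4 plans culture of all RLDT-positive stools and of a random 10% of RLDT-negative stools. For qPCR it says: "All RLDT-positive stool samples will be re-tested by qPCR". Section 3.2 gives neither result a role in the primary-care evaluation.

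**The concern.** Sensitivity and specificity for Shigella need a reference that stands for infection status. Here the reference is the index test itself, run by other staff. A stool that both laboratories misclassify is scored as correct. A stool that only the study laboratory misclassifies is scored as a hospital error. The four planned measures therefore describe how well hospital staff reproduce the study staff's result.

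The label conflicts with the rest of the article. The Discussion names a different gold standard for the same organism. Section 3.1 treats the reference-positive stools as children with Shigella, whereas under section 3.2 they are stools that the study staff read as RLDT-positive.

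What is at stake is the conclusion of the last aim in section 2.2. Figures reported as the sensitivity and specificity of the RLDT in primary care would be read as evidence that the test finds Shigella there, and they would feed the judgement on whether it can be used to detect and treat shigellosis. This comparison cannot supply that evidence.

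**Working it through.** **1. The plan's own figures (section 3.1).** Inputs: 225 stools, about 20% prevalence, 0.60 versus 0.80, two-sided exact binomial test, "target significance level set to 0.05" (at most 0.025 per tail).

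- Positives: 0.20 × 225 = 45. Negatives: 225 − 45 = 180.
- Sensitivity, n = 45: reject at 19 or fewer or 34 or more. Attained alpha is 0.0336 and power at 0.80 is 82.6%.
- Specificity, n = 180: reject at 94 or fewer or 122 or more. Attained alpha is 0.0397 and power at 0.80 is 99.996%.

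The article states: "The actual significance level achieved by the sensitivity test is 0.0336 and that achieved by the specificity test is 0.0397". Both levels reproduce exactly. The stated 80% power reads as at least 80%, and the stated 100% is a rounding. The arithmetic is sound; the question is what the 45 and 180 are.

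**2. What is estimated under section 3.2.** Let p be prevalence, Se and Sp the true accuracy of the study staff's RLDT, and se and sp that of the hospital staff's RLDT.

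- Study-positive share: P = p·Se + (1 − p)(1 − Sp).
- Reported sensitivity if errors are independent given true status: [p·Se·se + (1 − p)(1 − Sp)(1 − sp)] / P.
- Reported specificity likewise: [(1 − p)·Sp·sp + p(1 − Se)(1 − se)] / (1 − P).
- If all errors are shared, both equal 1 whatever Se and Sp are.

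**3. Illustration.** p = 0.20 is from section 3.1. The documents give no RLDT accuracy, so Se = 0.90 and Sp = 0.95 are assumed.

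P = 0.20 × 0.90 + 0.80 × 0.05 = 0.18 + 0.04 = 0.22.

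| Hospital laboratory | Reported sensitivity | Reported specificity |
|---|---|---|
| Always right about Shigella | 0.18/0.22 = 82% | 0.76/0.78 = 97% |
| Same accuracy, independent errors | (0.162 + 0.002)/0.22 = 75% | (0.722 + 0.002)/0.78 = 93% |
| Same accuracy, fully shared errors | 100% | 100% |

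In the last two rows the hospital's true sensitivity is 90%, yet the reported value is about 75% or 100%. With full agreement the report is 100% even if the assay's true sensitivity were 0.60.

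**4. Effect on the stated power.** Suppose 0.80 in section 3.1 means true sensitivity, both laboratories have 0.80 with specificity 0.95 (assumed), and errors are independent. Then P = 0.16 + 0.04 = 0.20, again 45 of 225. Reported sensitivity is (0.128 + 0.002)/0.20 = 65%. The chance of reaching 34 of 45 is then about 9%, not 82.6%. The stated power applies only if 0.80 is an agreement rate, which section 3.1 does not say.

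**5. The split.** Under section 3.2 the denominators follow the study RLDT's positivity rate, not disease prevalence. The two coincide in step 4. In step 3 the expected split is 0.22 × 225 = 49.5, or about 50 and 175.

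**6. Whether the other planned tests fill the gap.** qPCR on RLDT-positive stools shows what share of positives is confirmed. It says nothing about missed infections, so it gives neither sensitivity nor specificity. If the 10% culture rule were applied to the roughly 180 negatives here, about 18 would be cultured, by a method the Discussion calls insufficiently sensitive. If all 45 positives were true and detected, one culture-positive among those 18, weighted by 10, would move sensitivity from 100% to 45/55 = 82%. That would also mix two references.

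**The case against.** The strongest defence is that the comparison fits the aim. Sections 2.2 and 2.6 ask whether the test can be applied in a rural facility by trained and certified hospital staff, and the Introduction says the assay has already been evaluated in Asian and African countries. For the question of transfer to new operators, the study laboratory is a sensible comparator. The sentence in section 3.2 names that comparator openly, kappa is already planned, and percent agreement equals the planned sensitivity and specificity numerically. All of this stands. It means the fault is in the label, the sizing language and any accuracy conclusion, not in running the comparison.

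It is also fair that the size is assumed. The 75% end needs fully independent errors, whereas the same assay on the same stool may well fail in both laboratories for the same reason. The range shows what is possible and does not estimate the bias.

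A reader might infer that the reported figures will be far from the RLDT's true accuracy, or that they will flatter the test. The documents support neither: they give no RLDT accuracy, and the direction depends on whether errors are shared. A reader might also infer that the RLDT will never be compared with culture or qPCR. Section 2.4 plans both tests, and a condensed article need not describe every use of them.

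What the defence does not remove is the conflict between sections 3.1, 3.2 and the Discussion over what the reference represents.

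**Conclusion.** The point holds as a fault of labelling, sizing language and permitted conclusion. As written, sensitivity, specificity and predictive values in the primary-care evaluation are measures of operator agreement. They cannot support a claim about accuracy for Shigella, and calling the study RLDT the gold standard contradicts the Discussion and the disease-based wording of section 3.1. Under the assumed 0.90 and 0.95 at 20% prevalence, one true sensitivity of 90% could be reported as about 75% or as 100%. That range is illustrative and rests on those assumed values and on the two extremes of error dependence. The sample-size arithmetic is correct, and the hospitalization comparison and enrolment are not affected by this point.

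**What to change.** **Section 3.2.** Delete the gold-standard label. Report positive and negative percent agreement with the study laboratory, plus kappa as planned.

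**Section 3.1.** Restate 0.60 versus 0.80, and the power, as agreement rates among about 45 study-RLDT-positive and 180 study-RLDT-negative stools. Say that the split follows the study RLDT's positivity rate, not disease prevalence.

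**Conclusion.** Limit it to whether the test transfers to hospital staff. The qPCR already planned on RLDT-positive stools may be reported as the proportion of positives confirmed, but not as sensitivity or specificity.

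**If accuracy for Shigella is to be claimed.** Apply one independent reference to both the positive and the negative stools among the 225, and name it in sections 3.1 and 3.2. Weighting up the small cultured share of negatives is not a substitute, for the reasons in step 6 of the working.

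**Cost.** The core change is wording only and alters no planned number. The accuracy option needs added resources: if qPCR is the reference, up to about 180 further runs on the negative stools. The downside is that the headline becomes agreement rather than accuracy.
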